## Study procedures

### Practical implementation of the study

All study visits will be scheduled to coincide with the standard follow-up appointments. Each patient will have a maximum of 9 blood draws.

### Study information and pre-inclusion visit

All patients meeting the following criteria will be eligible for pre-inclusion in the PERCIMEL study before scheduled surgery, i.e.:Patient presenting with histologically confirmed cutaneous melanomaStage III, and staging has confirmed the absence of distant metastasis,with no detectable macroscopic lymph node involvement, and for whom there is an indication for completion lymph node biopsy and investigation of sentinel lymph node (Breslow > 0.8 mm, or regardless of Breslow index in the presence of ulceration)with macroscopically detectable lymph node involvement (either synchronously at the time of discovery of the melanoma, or metachronously) and with an indication for complete lymph node dissectionStage IV, and staging has confirmed the presence of distant metastasis, stage IV, amenable to complete resection, R0.

Information about the PERCIMEL study (and the associated biological collection) will be given to eligible patients by the clinicians in the participating centre during a medical consultation including:Complete clinical examination.Assessment of general state (WHO score) and body weightCollection of personal history of melanomaCollection of the results of staging examinations (radiological data): echography, abdominal-thoracic-pelvic CT scan, PET scan or brain CT scanCollection of pathology results with histological confirmation of cutaneous melanoma (from initial biopsy for diagnostic purposes)Collection of concomitant treatment (any treatment usually taken by the patient at the time of pre-inclusion)Check for eligibility criteria.

After sufficient time for reflection, and after obtaining the patient’s written informed consent, the patient will be pre-included.

### Surgery

Surgery will be performed according to standard practices in line with the recommendations for management of melanoma, and in general, within 28 days after the pre-inclusion visit.

For all pre-included patients:A blood draw of 30 ml for ctDNA analysis will be performed on the evening before, or on the day of surgery, before the start of surgery.Tissue samples (operative tumour samples and lymph nodes) will be retrieved and handled according to standard practices.

### Post-operative visit

For all pre-included patients, the post-operative visit will be performed within 2 to 3 weeks after surgery, and will consist in:Recording peri-operative complications (infected lymphocele, lymphoedema, scar disunion…) of grade > 2 or of any grade (according to the CTCAE classification version 5) if the impact on further management is significantA blood draw of 30 ml on the day of the post-operative visit for the purposes of the study.

### Inclusion visit

Patients will be definitively included if histology confirms:Positive lymph nodes for patients with stage III melanomaThe presence of metastasis for patients with stage IV melanoma

For all patients included, adjuvant therapy must be initiated within 12 weeks after surgery. Adjuvant therapy by immunotherapy or targeted therapy with BRAF and MEK inhibitors will be planned for 12 months, as per standard recommendations.

The inclusion visit will consist in:A clinical examination of the skin, scalp and lymph node basins, to note any signs and symptomsAssessment of general state (WHO score) and body weightBiology, including complete blood count, hemostasis, blood gases, plasma creatinine, liver function tests, and any other biological parameter required for the implementation of adjuvant medical therapy.Pathology results of the operative sample and/or sentinel lymph nodesRecording of any adverse events grade > 2 or adverse events of any grade (according to the CTCAE classification version 5) if the impact on medical therapy or further management is significantRecording of concomitant treatments (if there are any changes compared to those recorded at the pre-inclusion visit)A blood draw of 30 ml, performed on the day of the consultation where adjuvant therapy is initiated, and before the administration of adjuvant therapy.Patients who consented to pre-inclusion but who are not definitively included (negative sentinel lymph node, or metastasis not confirmed by lymph node dissection) will exit the study at this point and will be managed as per standard recommendations.

### Follow-up visits during adjuvant therapy (up to 12 months)

All follow-up visits will be scheduled to coincide with the standard follow-up appointments, i.e. every 3 to 4 months ± 2 weeks, in order to avoid the patient having to attend visits solely for the purposes of the study.

Each follow-up visit will include:Complete clinical examinationAssessment of general state (WHO score) and body weightBiology, including complete blood count, hemostasis, blood gases, plasma creatinine, liver function tests, and any other biological parameter required for the implementation of adjuvant medical therapy.Recording of any adverse events grade > 2 or adverse events of any grade (according to the CTCAE classification version 5) if the impact on medical therapy or further management is significantRecording of concomitant treatments (if there are any changes compared to those recorded at the pre-inclusion visit)Tumour assessmentA blood draw of 30 ml for ctDNA analysis, performed on the day of each follow-up visit

In case of relapse during the 12 months of follow-up, the patient will have one final 30 ml blood draw and will then exit the study.

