### Statistical analysis

The main objective is to evaluate the predictive value of the presence of ctDNA post-operatively on RFS. The RFS will be described by the Kaplan–Meier method, and compared according to the presence or absence of ctDNA post-surgery using the log rank test. A multivariate Cox regression model will be used to calculate the hazard ratio and 95% confidence interval (CI). As this is a cohort study, the results will be adjusted for baseline patient characteristics and the type of adjuvant therapy. To this end, bivariate analyses will be performed to identify variables related to the RFS. Variables yielding a *p*-value < 0.10, and the presence of ctDNA post-surgery will be included in the multivariate model. Results will be presented as hazard ratios with 95% CIs.

The same analysis will be performed for ctDNA presence pre-surgery, for the number of copies of mutant DNA per ml of plasma pre- and post-surgery, and for absolute and relative variations of the quantity of mutated DNA between pre- and post-surgery.

The impact of ctDNA evolution during follow-up on RFS will be evaluated using time-dependent survival models, by considering mutated DNA copy number as a time-dependent variable in the Cox model. This analysis will be adjusted for baseline patient characteristics and for the type of adjuvant therapy to assess whether the course of ctDNA during follow-up is an independent prognostic factor for survival.

To determine whether the predictive value of the course of ctDNA varies according to clinical and tumour characteristics at baseline, interaction tests will be performed.

Distant metastasis-free survival will be analysed using the same approach as for RFS. Melanoma-specific survival will also be analysed using the same approach, but considering death unrelated to the disease as a competing risk. Consequently, specific survival will be described as cumulative incidence according to the Kalbfleisch-Prentice method, and compared using Gray’s test. Bi- and multivariate analysis will be performed using the Fine and Gray subdistribution model.

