### Follow-up visits (from 12 to 24 months)

All follow-up visits will be scheduled to coincide with the standard follow-up appointments, in order to avoid the patient having to attend visits solely for the purposes of the study. Follow-up visits will be planned according to current guidelines. For the purposes of the study, a follow-up visit will be planned every 6 months ± 2 weeks.

Appropriate, systematic radiological examination (CT or PET scan) is recommended every 6 months during the 12 months of follow-up.

Each follow-up visit will consist in:Complete clinical examinationAssessment of general state (WHO score) and body weightRecording of any adverse events grade > 2 or adverse events of any grade (according to the CTCAE classification version 5) if the impact on medical therapy or further management is significantRecording of concomitant treatments (if there are any changes compared to those recorded at the pre-inclusion visit)Tumour assessmentA blood draw of 30 ml for ctDNA analysis, performed on the day of each follow-up visit

After the 12 months of follow-up, the patient will have one final blood draw and will then exit the study.

In case of relapse during the 12 months of surveillance, the patient will have one final blood draw and will then exit the study.

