### Tumour assessment

Tumour assessment will include:Clinical examinationCT or PET scan or brain CT scanBiology, including measurement of LDH

Tumour assessment will be scheduled every 3 to 4 months ± 2 weeks during adjuvant therapy and every 6 months ± 2 weeks during follow-up, according to local practices in each centre.

Progressive disease is defined as the appearance of a new clinical or radiological lesion.

In case of progressive disease, the visit will consist in:A clinical examination of the skin, scalp and lymph node basins, to note any signs and symptomsAssessment of general state (WHO score) and body weightBiology, including complete blood count, hemostasis, blood gases, plasma creatinine, liver function testsRecording of any adverse events grade > 2 or adverse events of any grade (according to the CTCAE classification version 5) if the impact on medical therapy or further management is significantRecording of concomitant treatments (if there are any changes compared to those recorded at the pre-inclusion visit)Recording of the tumour assessment performed prior to the follow-up or surveillance visitA final blood draw of 30 ml

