### Premature withdrawal from the study

The following reasons may justify premature withdrawal of a patient from the study:Failure to perform post-operative blood testsPatient not eligible for treatment with immunotherapy using an anti-PD1 monoclonal antibody or targeted therapy using BRAF and MEK inhibitors in the adjuvant settingProgressive diseaseDeath of the patientWithdrawal of consent

Specific case of patients who:Present major toxicity requiring definitive discontinuation of adjuvant therapyPresent toxicity requiring postponement of treatment or reduced treatment doseRefuse to pursue adjuvant therapy

These patients will be maintained in the study, and blood draws will continue to be performed up to 24 months after initiation of adjuvant therapy, with the patient’s consent.

Participants in the study may withdraw their consent at any time without justification, for whatever reason, and this will in no way affect their right to continue to be treated by their physician.

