### Secondary endpoints

Recurrence-free survival (RFS) is defined as the time from inclusion to loco-regional relapse, distant metastasis or all-cause death, whichever occurs first.Distant metastasis-free survival is defined as the time from inclusion to distant metastasis or all-cause death, whichever occurs first.Melanoma specific survival is defined as the time from inclusion to cancer-related death.

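### Patients leave the study at first relapse, so melanoma-specific survival has almost no observable events and distant metastasis-free survival is informatively censored

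*Protocol article*

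**What the plan says.** Both follow-up sections of the protocol article end participation at relapse. During adjuvant therapy, "the patient will have one final 30 ml blood draw and will then exit the study". For months 12 to 24: "In case of relapse during the 12 months of surveillance, the patient will have one final blood draw and will then exit the study".

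The Tumour assessment section does not separate loco-regional from distant relapse: "Progressive disease is defined as the appearance of a new clinical or radiological lesion". Progressive disease also appears in the list introduced by "The following reasons may justify premature withdrawal of a patient from the study". That section has a retention rule, but only for patients with toxicity or who refuse adjuvant therapy. For them, "blood draws will continue to be performed up to 24 months after initiation of adjuvant therapy". Relapsed patients are not covered by it.

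The Secondary endpoints section gives these definitions:

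- "Distant metastasis-free survival is defined as the time from inclusion to distant metastasis or all-cause death, whichever occurs first"
- "Melanoma specific survival is defined as the time from inclusion to cancer-related death"

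Under Statistical analysis, "Distant metastasis-free survival will be analysed using the same approach as for RFS", that is, Kaplan–Meier, log-rank and Cox. Melanoma-specific survival is to be analysed by cumulative incidence, Gray's test and a Fine and Gray model, with unrelated death as the competing risk. No section describes collecting vital status, cause of death or distant metastasis after a patient has exited.

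**The concern.** Recurrence-free survival is complete at first relapse. The other two survival endpoints are not. Death from melanoma ordinarily follows a recorded recurrence, so exit at recurrence removes nearly all the events of interest. What remains for the Fine and Gray model is mainly unrelated death and censoring.

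Loco-regional relapse is not an event for distant metastasis-free survival, so a patient who exits then is censored just as the risk of distant spread rises. That breaks the independent-censoring assumption behind Kaplan–Meier, log-rank and Cox. The trial's hypothesis is that ctDNA-positive patients relapse more, so the censoring also depends on the marker under study. An analysis plan cannot repair this, because the missing data would never have been collected.

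**Working it through.** **Inputs from the protocol article (Sample size calculation).** N = 124 analysable; 25% ctDNA-positive; hazard ratio 2.5; 24-month recurrence-free survival 70%; alpha 5%; power 90%.

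**Assumptions, not in the document.** Exponential times; the loco-regional share of first events; the time from loco-regional relapse to distant metastasis; survival after relapse; the share of first events that are melanoma deaths with no earlier recorded relapse.

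**1. The plan's own figure.** Freedman's formula with unequal groups, k = 0.25/0.75 = 1/3, two-sided 5%:

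events = 10.51 × (1 + 2.5/3)² / [(1/3) × 1.5²] = 47.1

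Take 70% as the ctDNA-negative figure. Positives then have 0.70^2.5 = 41%, and the pooled event probability is 0.75 × 0.30 + 0.25 × 0.59 = 0.3725. N = 47.1/0.3725 = 126, against 124 stated, so the figure is reproduced to within 3%. It is not in dispute.

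**2. Who reaches a first event by month 24.** If 70% is the overall figure, 124 × 0.30 = 37 patients. If it is the ctDNA-negative figure, 93 × 0.30 + 31 × 0.59 = 28 + 18 = 46. On the second reading, 59% of positives and 30% of negatives have a first event. All whose event is a relapse then exit. Steps 3 and 4 use the lower count, 37.

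**3. Melanoma-specific survival.**

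- As written, only melanoma deaths with no earlier recorded relapse can be seen. At an assumed 0–5% of first events: 37.2 × 0 to 37.2 × 0.05 = 0 to 1.9.
- With follow-up to month 24, treat first events as relapses. Let λ = −ln(0.70)/24 = 0.01486 per month and μ = ln 2 / (median survival after relapse). Deaths by month 24 = 124 × {0.30 − λ(0.70 − e^(−24μ))/(μ − λ)}.

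| Median survival after relapse | Deaths by month 24 |
|---|---|
| 12 months | 17.9 |
| 24 months | 10.9 |
| 48 months | 6.1 |

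**4. Distant metastasis-free survival.** Let p be the loco-regional share of first events, and now μ = ln 2 / (median time from loco-regional relapse to distant metastasis).

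- Censored at loco-regional relapse: 124 × 0.30 × p
- Events still seen: 124 × 0.30 × (1 − p)
- Events lost: 124 × p × {0.30 − λ(0.70 − e^(−24μ))/(μ − λ)}
- True 24-month value: 1 − (seen + lost)/124
- Value estimated with censoring at loco-regional relapse: 0.70^(1 − p)

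| p | Median to distant | Censored | Seen | Lost | Share lost | True | Estimated | Overstated by |
|---|---|---|---|---|---|---|---|---|
| 30% | 24 mo | 11.2 | 26.0 | 3.3 | 11% | 0.764 | 0.779 | 1.5 points |
| 30% | 12 mo | 11.2 | 26.0 | 5.4 | 17% | 0.747 | 0.779 | 3.2 points |
| 50% | 24 mo | 18.6 | 18.6 | 5.5 | 23% | 0.806 | 0.837 | 3.1 points |
| 50% | 12 mo | 18.6 | 18.6 | 8.9 | 32% | 0.778 | 0.837 | 5.9 points |

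With wider assumptions (p = 20–50%, median 6 to 24 months), 7 to 19 patients are censored and 2 to 13 distant metastases are lost.

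**The case against.** **The primary analysis is untouched.** First relapse is itself a recurrence-free survival event, and the sample size rests on that endpoint. This is correct. The damage is confined to secondary endpoints.

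**Exit may not mean the end of data capture.** The withdrawal list says only that its reasons may justify withdrawal, and it includes death, which is an endpoint event. The surveillance section also uses the exit wording for patients who complete 24 months. The article condenses a full protocol that is not shown and that could collect vital status passively. This is possible. But the two follow-up sections state exit at relapse as a rule without exception, and a retention rule was written for other patients and not for these. If the full protocol does otherwise, the article's sentences are wrong and need correcting.

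**Melanoma-specific survival would be thin anyway.** Full follow-up to month 24 gives only about 6 to 18 deaths, so an adjusted Fine and Gray model would stay weak. This stands, but a cumulative incidence curve from 6 to 18 deaths can be reported, and one from 0 to 2 cannot be used.

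**The marker's hazard ratio may move little.** Take a hazard ratio of 2.5 on first events, 70% as the ctDNA-negative figure and no ctDNA effect after loco-regional relapse. The Cox hazard ratio for distant metastasis-free survival is then 2.5 with censoring at relapse and 2.29 to 2.40 with complete follow-up, so the censored analysis is 4–9% higher. On those inputs the bias falls mainly on the absolute estimate. If ctDNA also influences the course after relapse, the distortion could differ, and the data to check this would not exist.

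**Conclusion.** The concern holds. As written, the follow-up rule and two of the three survival endpoints are incompatible.

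- **Melanoma-specific survival** cannot be estimated: about 0 to 2 observable events, with roughly 6 to 18 deaths by month 24 going unseen.
- **Distant metastasis-free survival** can be computed from 19 to 26 observed events, but it is biased upwards. About 11–32% of its events are lost, and the 24-month value is overstated by 1.5 to 5.9 points.

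The incompatibility follows from the text alone. The sizes rest on exponential times, an overall 24-month recurrence-free survival of 70%, and the assumed loco-regional share, lag to distant spread and survival after relapse. The primary recurrence-free survival analysis and the sample size stand.

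**What to change.** Reword both follow-up sections so that relapse ends the study blood draws, not follow-up. In the withdrawal list, remove progressive disease or restate it as the end of sampling. For every included patient, record from routine care, up to 24 months after inclusion, the date of first distant metastasis, the date of death and the cause of death. For patients who have already exited, retrieve the same items from records where consent allows.

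If the full protocol already collects these data, correct the article's exit wording to say so.

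If the sponsor will not collect them, drop melanoma-specific survival. Replace distant metastasis-free survival with distant metastasis as first event, labelled as such, with loco-regional relapse treated as a competing event rather than as censoring.

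The cost is a protocol amendment, a check that consent covers data collection after relapse, a few case report form fields and a vital-status check. No visit, sample or patient is added. The article says an amendment is already in preparation for the neoadjuvant strategy, so this change could go with it.

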### Follow-up visits (from 12 to 24 months)

All follow-up visits will be scheduled to coincide with the standard follow-up appointments, in order to avoid the patient having to attend visits solely for the purposes of the study. Follow-up visits will be planned according to current guidelines. For the purposes of the study, a follow-up visit will be planned every 6 months ± 2 weeks.

Appropriate, systematic radiological examination (CT or PET scan) is recommended every 6 months during the 12 months of follow-up.

Each follow-up visit will consist in:Complete clinical examinationAssessment of general state (WHO score) and body weightRecording of any adverse events grade > 2 or adverse events of any grade (according to the CTCAE classification version 5) if the impact on medical therapy or further management is significantRecording of concomitant treatments (if there are any changes compared to those recorded at the pre-inclusion visit)Tumour assessmentA blood draw of 30 ml for ctDNA analysis, performed on the day of each follow-up visit

After the 12 months of follow-up, the patient will have one final blood draw and will then exit the study.

In case of relapse during the 12 months of surveillance, the patient will have one final blood draw and will then exit the study.

### Tumour assessment

Tumour assessment will include:Clinical examinationCT or PET scan or brain CT scanBiology, including measurement of LDH

Tumour assessment will be scheduled every 3 to 4 months ± 2 weeks during adjuvant therapy and every 6 months ± 2 weeks during follow-up, according to local practices in each centre.

Progressive disease is defined as the appearance of a new clinical or radiological lesion.

In case of progressive disease, the visit will consist in:A clinical examination of the skin, scalp and lymph node basins, to note any signs and symptomsAssessment of general state (WHO score) and body weightBiology, including complete blood count, hemostasis, blood gases, plasma creatinine, liver function testsRecording of any adverse events grade > 2 or adverse events of any grade (according to the CTCAE classification version 5) if the impact on medical therapy or further management is significantRecording of concomitant treatments (if there are any changes compared to those recorded at the pre-inclusion visit)Recording of the tumour assessment performed prior to the follow-up or surveillance visitA final blood draw of 30 ml

### Study stopping rules

The study may be suspended or discontinued by the sponsor, in consultation with the coordinator, or at the request of the competent authorities and/or the Ethics Committee (Comité de Protection des Personnes) if patient accrual is insufficient.

### Premature withdrawal from the study

The following reasons may justify premature withdrawal of a patient from the study:Failure to perform post-operative blood testsPatient not eligible for treatment with immunotherapy using an anti-PD1 monoclonal antibody or targeted therapy using BRAF and MEK inhibitors in the adjuvant settingProgressive diseaseDeath of the patientWithdrawal of consent

Specific case of patients who:Present major toxicity requiring definitive discontinuation of adjuvant therapyPresent toxicity requiring postponement of treatment or reduced treatment doseRefuse to pursue adjuvant therapy

These patients will be maintained in the study, and blood draws will continue to be performed up to 24 months after initiation of adjuvant therapy, with the patient’s consent.

Participants in the study may withdraw their consent at any time without justification, for whatever reason, and this will in no way affect their right to continue to be treated by their physician.

